### Eligibility

Inclusion and exclusion criteria for patients with PD are summarized in Textbox 1.

Since patients with early-stage PD typically show a good response to anti-Parkinson agents such as levodopa [20], it is challenging to isolate and evaluate the additional effects of acupuncture and moxibustion in this population. Therefore, this study included patients who have been taking anti-Parkinson agents for more than 5 years or who were at Hoehn and Yahr stage 2-3, representing the midstage or beyond. Inclusion and exclusion criteria for healthy participants are summarized in Textbox 2.

Dropout criteria are summarized in Textbox 3.

Inclusion and exclusion criteria for patients with Parkinson disease (PD).

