**Inclusion criteria**
Men and women aged 50-85 yearsParticipants who have no problems with cognitive function and who have voluntarily agreed to participate in the study through written consentParticipants who selected to match the “Patients with PD” group with age, sex, and other health conditions, excluding the diagnosis of Parkinson disease (PD)

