#### Evaluation of Gut Microbiome–Related Metabolites and Gut Microbiome Change

Blood samples will be used to assess changes in gut microbiome–related metabolites. Blood will be collected from participants after an 8-hour fast before blood collection, and changes in metabolites will be determined using liquid chromatography-mass spectrometry and gas chromatography-mass spectrometry analyses. Western blotting will be applied to confirm changes in strain-derived factors in the blood of patients with PD. Participants’ fecal samples will be used to analyze the composition of the gut microbiome using 16S rRNA sequencing and fecal microbiome transplantation to assess the correlation between gut microbiome and response to acupuncture treatment. A small amount of feces will be collected using 4N6 FLOQSwabs (Copan Diagnostics Inc). For participants with PD, 2-3 g of feces will be collected using a Stool Collection Tubes With DNA Stabilizer (Invitek Diagnostics) for fecal microbiome transplantation. A FastDNA SPIN Kit for Feces (MP Biomedicals) will be used to isolate DNA from feces for DNA extraction and sequencing. DNA will be subjected to polymerase chain reaction targeting the V3-V4 variable region of bacterial 16S rRNA as a template, followed by sequencing library construction and sequencing reactions on the MiSeq Platform (Illumina, Inc). Sampling will be conducted at day 0, 6 weeks, 12 weeks, and 20 weeks in participants with PD and after screening in healthy participants.

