#### Changes in Gut Microbiome–Related Metabolites and Gut Microbiome

Differences in microbiome at each time point will be measured using weighted-unweighted UniFrac distance metrics and subsequently tested using analysis of similarity (ANOSIM). Correlations of clinical outcomes and treatment effects with key microbiomes will be analyzed using Spearman rank correlation analysis, with *P*<.05 considered significant. Principal component analysis will be applied to analyze metabolite distribution in the sample. Partial least squares-discriminant analysis will be applied to identify differences between patients with PD and healthy participants when analyzing metabolite distributions. Selected gut microbiome and metabolite changes will be analyzed by 1-way repeated measures ANOVA, with significant differences between time points determined at *P*<.05. The pathway analysis or enrichment analysis will be performed to analyze the metabolic pathways of the selected metabolites. The Kyoto Encyclopedia of Genes and Genomes database [39] will be used to identify interactions between metabolites. Receiver operating characteristic analysis will be conducted to confirm whether the selected metabolites reflect the representativeness of the disease or treatment.

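### The PD-versus-healthy metabolite contrast cannot tell disease from long-term anti-Parkinson medication, so the ROC step cannot confirm that selected metabolites represent the disease

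*Protocol article*

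**What the plan says.** Textbox 1 (inclusion criteria for patients with PD) lists use of anti-Parkinson agents for more than 5 years, anticholinergics aside, and Hoehn and Yahr stage 2-3 as separate entries. The paragraph under Eligibility that explains this choice describes the population as "patients who have been taking anti-Parkinson agents for more than 5 years or who were at Hoehn and Yahr stage 2-3", which joins the two with an alternative. Textbox 2 defines healthy participants as people without a PD diagnosis, matched to the patients on age, sex and other health conditions. It does not mention anti-Parkinson drugs.

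Under Evaluation of Gut Microbiome–Related Metabolites and Gut Microbiome Change, blood is analysed by "liquid chromatography-mass spectrometry and gas chromatography-mass spectrometry analyses". The stated sampling condition is an 8-hour fast.

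The analysis section on metabolites and microbiome then says "Partial least squares-discriminant analysis will be applied to identify differences between patients with PD and healthy participants when analyzing metabolite distributions". Selected metabolites also go to pathway analysis and repeated measures ANOVA. Finally, "Receiver operating characteristic analysis will be conducted to confirm whether the selected metabolites reflect the representativeness of the disease or treatment".

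The limitations in the Discussion name diet as an influence on the PD-versus-healthy microbiome comparison, and levodopa dose adjustment as a possible confounder of the microbiome. They do not mention medication in connection with the PD-versus-healthy metabolite contrast.

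**The concern.** Under Textbox 1 every patient is a long-term user of anti-Parkinson drugs. The comparators have no PD indication for them. Their exposure is near zero by inference, since Textbox 2 does not name the drugs. A metabolite can then separate the groups because of the disease, because it is a drug or drug breakdown product, or because the drug has shifted an endogenous or microbial compound. The group comparison sees only the total.

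The plan nevertheless treats good discrimination as confirmation that a metabolite represents the disease. A pure drug marker would pass that check. At stake is whether the published marker list and its pathway interpretation describe PD or its treatment with medication. The primary outcome, MDS-UPDRS, is not touched.

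**Working it through.** The plan gives no effect size, AUC or calculated sample size for this contrast, so there is no figure to reproduce. The inputs are 60 patients and 20 healthy participants (Sample Size), the entry criteria (Textboxes 1 and 2), and assumed drug-signal strengths.

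**1. Identifiability.** Write a metabolite's mean as μ + β·(PD) + γ·(drug exposure), each indicator 0 or 1. If exposure is 1 in all patients and 0 in all healthy participants, the two indicators are the same column. The group difference is β + γ, and no adjustment for exposure can split it. If a share f of patients is exposed, the difference is β + f·γ. It still contains the drug term.

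**2. A feature present only through the drug.** Suppose it is detected in a share d of PD samples and in no healthy sample. With ties counted as one half,

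AUC = d × 1 + (1 − d) × 0.5 = 0.5 + d/2.

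- d = 0.6: 0.5 + 0.30 = 0.80
- d = 0.8: 0.5 + 0.40 = 0.90
- d = 1.0: 0.5 + 0.50 = 1.00

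The documents do not give d; these values are assumptions.

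**3. A continuous feature shifted by the drug.** For a shift of δ standard deviations in all patients and none in healthy participants, AUC = Φ(δ/√2). This gives 0.64, 0.76, 0.92 and 0.98 for δ = 0.5, 1, 2 and 3.

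**4. Ranking in PLS-DA.** The check was a simulation with 60 versus 20 participants, 200 independent features, no disease effect in any of them, and 5 features shifted by δ in exposed patients. It used one-component PLS-DA ranked by variable importance, with 400 repetitions. The feature counts, δ, the exposed share and the ranking rule are all assumptions.

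| δ (SD) | Drug features in top 5, all exposed | AUC of top feature | Drug features in top 5, 80% exposed | AUC of top feature |
|---|---|---|---|---|
| 0.5 | 33% | 0.74 | 20% | 0.72 |
| 1 | 84% | 0.83 | 62% | 0.78 |
| 2 | 100% | 0.96 | 98% | 0.88 |
| 3 | 100% | 0.99 | 100% | 0.92 |

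With no drug signal at all, the top feature still had an AUC of about 0.72, from selection alone. Strong drug features therefore dominate the ranking. Weak ones (0.5 SD) take a minority of the top places.

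**5. The two wordings of the criterion.** The 80% columns show what happens if exposure is incomplete, as the Eligibility paragraph might allow. That figure is illustrative. A patient admitted on stage with less than 5 years of drug use may still be medicated.

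**The case against.** The strongest reply has four parts.

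*The assay is not described in enough detail.* The blood endpoint is called gut microbiome–related metabolites, and whether the panel is targeted or untargeted is not stated. The plan also does not say that PLS-DA ranking is the selection rule. A reader might infer that drug compounds will head the list. The documents do not support that. A restricted panel would reduce direct drug features, and at a 0.5 SD shift most top places in the simulation were not drug features. What stands is that such features may be selected.

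*Feature annotation is laboratory detail.* A condensed article may leave the removal of exogenous compounds to another document, so its absence here is not an error in itself. But the entry criteria, the contrast and the disease reading of the ROC are all stated. A filter held elsewhere would not make that reading valid, because drug-induced shifts in endogenous or microbial metabolites would remain.

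*Exposure may not be complete.* A reader might take it as settled that every patient is a long-term user. That follows from Textbox 1 only; the Eligibility paragraph says otherwise.

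*Change over time is within-patient.* A reader might conclude that the 20-week course will follow dosing and not acupuncture. That does not follow from between-group confounding. A stable regimen creates no time trend, and irregular time since last dose adds noise unless it shifts systematically between visits. Levodopa daily dose and number of doses are assessed at day 0 and at 6, 12 and 20 weeks, and the Discussion asks that significant dose changes be considered.

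It is also fair that the study is exploratory and that the choice of medicated patients is deliberate and explained.

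**Conclusion.** The point holds as a limit on inference. With the Textbox 1 criteria, the PD-versus-healthy PLS-DA and the ROC cannot distinguish disease from medication, so a high AUC does not confirm that a metabolite represents the disease. A drug-only feature could reach an AUC of 0.80 to 1.00 for d between 0.6 and 1.0. How many such features would actually be selected cannot be determined from the article. It depends on the panel, the selection rule and the drug signal, and the simulated share of the top 5 ran from 20% to 100% over the assumptions tried.

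The conclusion assumes near-zero use of these drugs among healthy participants and near-complete use among patients. It weakens, but does not disappear, at 80% exposure. It concerns a secondary, exploratory analysis and is worth correcting because the stated interpretation is unsupported and the correction is cheap.

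**What to change.** 1. Before PLS-DA, pathway analysis and ROC, exclude features annotated as anti-Parkinson drugs or their known metabolites, using the medication recorded at screening. List the excluded features separately.
2. Within PD at day 0, report the correlation of each selected metabolite with recorded levodopa daily dose, and flag those that track dose. Treat this as a flag, not a test of origin. With 60 patients, the 95% interval around a zero correlation reaches about tanh(1.96/√57) = 0.25 either way, so a small observed correlation does not clear a feature. Dose may also track disease severity.
3. State the conclusion as *medicated PD versus healthy participants*, not as representing the disease. Attach the same interpretive caveat to the baseline microbiome contrast.
4. Reconcile the Eligibility paragraph with Textbox 1, and report how many patients were on anti-Parkinson drugs and for how long.
5. For time-course results, note any systematic shift between visits in levodopa dose and, where it was recorded, in time since last dose.

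The article reports that recruitment and observation have ended and analysis is under way. Items 1 to 3 need no new samples: one annotation filter, one set of within-group correlations and changed wording. The cost is that some genuine features sharing a drug pathway may be filtered or flagged, which is why they should be listed. The filter does not remove drug-induced shifts in endogenous or microbial metabolites, so item 3 is needed whatever the panel.

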### Sample Size

This study is not intended to statistically validate the intervention effect of acupuncture and moxibustion on PD but was rather conducted as an exploratory study comparing gut microbiome markers in patients with PD and healthy participants and the effects of acupuncture and moxibustion on the gut microbiome in patients with PD. Therefore, the sample size required for the study will be 60 patients with PD and 20 healthy individuals, depending on the financial resources and study environment, and in consultation with experts in gut microbiology.

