#### Comparative Analysis of the Gut Microbiome Between Healthy Participants and Patients With PD

Differences in gut microbiome between healthy participants and patients with PD will be determined by testing the acquired data for normality and performing a parametric test with an independent *t* test if the population is normal or a nonparametric test with the Mann-Whitney *U* test if the population is not normal.

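### PLS-DA is the only method named for finding PD-versus-healthy metabolite differences, and it has no stated error control; its fitted separation is not evidence of a difference

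*Protocol article*

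**What the plan says.** The statistical section on changes in metabolites and gut microbiome (Protocol article) states: "Partial least squares-discriminant analysis will be applied to identify differences between patients with PD and healthy participants when analyzing metabolite distributions". It gives no number of components, decision rule, cross-validation or permutation test.

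The other methods named nearby do not cover this contrast:
- Principal component analysis describes how metabolites are distributed and does not use the groups.
- The repeated-measures ANOVA compares time points. Healthy participants have only one: "Sampling will be conducted at day 0, 6 weeks, 12 weeks, and 20 weeks in participants with PD and after screening in healthy participants".
- The t test or Mann-Whitney rule, in the section comparing healthy participants with patients, is worded for the microbiome only: "Differences in gut microbiome between healthy participants and patients with PD will be determined by testing the acquired data for normality".
- The ROC step works on metabolites that have already been chosen: "Receiver operating characteristic analysis will be conducted to confirm whether the selected metabolites reflect the representativeness of the disease or treatment".

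On size, the Sample Size section says "the sample size required for the study will be 60 patients with PD and 20 healthy individuals, depending on the financial resources and study environment". The same section calls the study exploratory. On measurement, "changes in metabolites will be determined using liquid chromatography-mass spectrometry and gas chromatography-mass spectrometry analyses"; the number of metabolites is not given.

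**The concern.** PLS-DA is a supervised method. It looks for the direction in the metabolite data that covaries most with the labels and then shows the groups along that direction. Some separation is therefore built in. Without validation, the score plot, the fitted AUC and a test on the fitted scores cannot distinguish a real difference from chance.

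The same statistical section names a test or a P<.05 threshold for the microbiome distances (ANOSIM), the Spearman correlations and the repeated-measures ANOVA. The PD-versus-healthy metabolite contrast has neither. If fitted separation were read as the result, a difference could be announced when none exists. Any pathway or ROC result built on metabolites ranked that way would inherit the error. The limitations in the Discussion mention type II error from the sample size but not this false-positive risk.

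**Working it through.** The plan has no figure of its own to reproduce: the sample size rests on feasibility, and no error rate is stated for PLS-DA. The check is therefore how PLS-DA behaves when there is no difference.

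**Inputs.** From the Sample Size section: 60 + 20 = 80 participants, hence 80 baseline samples. Assumed, because not stated: number of features p from 20 to 1000, two components, Gaussian autoscaled features, either independent or in blocks of 10 with correlation 0.5.

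**Why fitted separation is guaranteed.** With X the scaled data and y the centred label, the first PLS weight is w = X'y/‖X'y‖ and the score is t = Xw. Then y't = y'XX'y/‖X'y‖ = ‖X'y‖, which is positive unless every feature is exactly uncorrelated with the label. For independent null features, the squared correlation of t with y is roughly p/(p + n − 1):
- p = 20: 20/(20 + 79) = 0.20
- p = 100: 100/(100 + 79) = 0.56
- p = 1000: 1000/(1000 + 79) = 0.93

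A two-group t test on 80 scores (78 degrees of freedom, critical t 1.99) reaches P<.05 once the squared correlation exceeds 1.99²/(1.99² + 78) = 0.048. The null expectation is above that even at p = 20.

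**Simulation under no difference** (60 against 20, two-component PLS-DA, 200 data sets per setting; each cell gives independent / correlated features):

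| p | Mean fitted AUC | Fitted AUC > 0.9 | Perfect separation | First score P<.05 | Mean 7-fold cross-validated AUC |
|---|---|---|---|---|---|
| 20 | 0.82 / 0.80 | 2.5% / 0.5% | 0% / 0% | 100% / 90.5% | 0.50 / 0.50 |
| 50 | 0.95 / 0.90 | 96% / 49% | 0% / 0% | 100% / 100% | 0.50 / 0.48 |
| 100 | 0.997 / 0.96 | 100% / 99.5% | 41.5% / 0% | 100% / 100% | 0.49 / 0.52 |
| 200 | 1.000 / 0.995 | 100% / 100% | 100% / 22% | 100% / 100% | 0.51 / 0.50 |
| 500 | 1.000 / 1.000 | 100% / 100% | 100% / 100% | 100% / 100% | 0.50 / 0.50 |
| 1000 | 1.000 / 1.000 | 100% / 100% | 100% / 100% | 100% / 100% | 0.51 / 0.49 |

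**With error control.** A 99-permutation label test at nominal 5%, run on fitted R2Y with correlated features, rejected in 5.5% (p = 100) and 4.0% (p = 500) of null data sets. It holds its level because permuted labels are refitted in the same way as the real ones; the same argument applies when the statistic is cross-validated AUC or Q2, a version not simulated here. Mean Q2 was negative at every p (−0.07 to −0.61). Even so, Q2 > 0 occurred in 0% to 25% of null data sets, most often at p = 1000 with independent features, so a bare Q2 > 0 rule does not control the error.

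**Precision.** 200 out of 200 is compatible with a true rate down to about 0.025^(1/200) = 98%. The permutation sizes carry about ±1.96 × √(0.05 × 0.95/200) = ±3 percentage points.

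**The case against.** The strongest reply is that silence is not error. A journal article condenses the full protocol, and validation of a multivariate model is the kind of detail that may sit there. This stands in part. A reader might infer that the step can never return a finding of no difference; the text does not support that, because it neither makes fitted separation the criterion nor rules out cross-validation or permutation.

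Three further readings are tempting and also go too far:
- That 80 samples alone ensure separation in essentially every data set. This depends on the unstated number of metabolites. At 20 features, separation was never complete and fitted AUC above 0.9 was rare; at 50 correlated features it occurred in about half of data sets. Correlation among features also delays perfect separation (22% against 100% at p = 200).
- That the assay is untargeted. The article does not say so, and a limited panel is compatible with its wording.
- That PLS-DA picks the metabolites for the later ANOVA, pathway and ROC steps. The article says "The pathway analysis or enrichment analysis will be performed to analyze the metabolic pathways of the selected metabolites" without stating how they are selected.

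Nor is a t test on first-component scores planned; it serves here only to measure how strongly the fit favours separation. The exploratory label lowers the stakes, but exploration still has to tell signal from noise.

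What the reply does not remove is that a supervised fit is the named means of identification and nothing else is named for this contrast. The problem lies in the method chosen for that role as well as in detail left out.

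**Conclusion.** The point holds in conditional form. The article gives PLS-DA the job of identifying PD-versus-healthy metabolite differences with no stated error control and no alternative test. Fitted separation cannot carry that conclusion. With no true difference, first-component scores differ at P<.05 in about 90% to 100% of data sets across 20 to 1000 features, and fitted AUC passes 0.9 in nearly all data sets from about 100 features, though rarely at 20.

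The size rests on assumptions the article does not settle: the number of metabolites, two components, and Gaussian features. It is the error rate that would follow if fitted separation were the criterion, and should not be read as the error rate of a validated analysis. Validation removes the artefact: cross-validated AUC averages about 0.5, and a permutation test rejects in about 5% of null data sets.

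**What to change.** In the statistical section on changes in metabolites and gut microbiome, limit PLS-DA to display and ranking, and add a decision rule. Declare a PD-versus-healthy metabolite difference only if cross-validated performance (AUC or Q2, one of them named in advance) exceeds the 95th percentile of the same statistic over at least 1000 label permutations. Scaling and the choice of components belong inside the folds, and the whole procedure is repeated for each permutation. State that Q2 > 0 alone is not sufficient.

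If the test fails, report any metabolites ranked by PLS-DA, and any pathway or ROC results built on them, as unsupported.

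The article reports that recruitment and observation have ended and analysis is under way, so no data collection changes. The cost is wording and slightly more computing. The downside is that some apparent separations can no longer be reported as differences.

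### The ROC step cannot confirm metabolites for PD versus healthy when only one cohort is available both to select and to test them

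*Protocol article*

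**What the plan says.** The section on changes in gut microbiome–related metabolites and gut microbiome lists a sequence of analyses. After a principal component analysis, a supervised method is applied: "Partial least squares-discriminant analysis will be applied to identify differences between patients with PD and healthy participants when analyzing metabolite distributions". Change over time is then tested on a reduced set: "Selected gut microbiome and metabolite changes will be analyzed by 1-way repeated measures ANOVA, with significant differences between time points determined at *P*<.05". Pathway analysis follows, and the last step is the ROC: "Receiver operating characteristic analysis will be conducted to confirm whether the selected metabolites reflect the representativeness of the disease or treatment".

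The material for all of this is one group of people. Under Sample Size, "the sample size required for the study will be 60 patients with PD and 20 healthy individuals". Under the evaluation of metabolites and microbiome, "Sampling will be conducted at day 0, 6 weeks, 12 weeks, and 20 weeks in participants with PD and after screening in healthy participants". The platform is mass spectrometry: "changes in metabolites will be determined using liquid chromatography-mass spectrometry and gas chromatography-mass spectrometry analyses".

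The article does not give the number of metabolites, the rule by which metabolites become selected, the two classes of the treatment ROC, or an AUC criterion. It mentions no split sample or external cohort. The Discussion lists several limitations (no PD control group, sample size, no blinding, adverse event assessment, diet, levodopa dosage), but not this one.

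**The concern.** An ROC confirms a marker only if the data that produce the AUC had no part in choosing the marker. Here the disease label (PD or healthy) guides the PLS-DA, and the same label in the same 80 people would define the disease ROC. A metabolite picked because it differs between these two samples will show an AUC above 0.5 in these two samples, whether or not it differs in the population. The AUC then carries the optimism of the selection, and no part of the stated plan removes it.

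What is at stake is the claim attached to the result. A list of metabolites reported as confirmed by ROC would be read as validated markers of PD or of response to treatment, and the Discussion intends to present positive findings as first clinical evidence for a mechanism. Some or all of the list could be noise.

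**Working it through.** The plan has no AUC, power figure or metabolite count to reproduce, so the check asks what the ROC step would return if no metabolite differed at all (true AUC 0.50).

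**Inputs from the article:** 60 PD and 20 healthy; PD sampled at four time points, healthy once; P<.05 for the time comparisons.

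**Assumptions:** 50 to 1000 independent, normally distributed metabolites; selection at P<.05 on the contrast in question; within-patient correlation 0 to 0.7.

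**1. Will noise be selected?** The chance of at least one false selection among m metabolites is 1 − 0.95^m: 92% for m = 50, 99.4% for 100 and above 99.99% for 200. The expected number selected is 0.05m, that is 2.5, 5 and 10.

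**2. AUC of selected noise, PD versus healthy.**
- Mean absolute z given |z| > 1.96: 2 × φ(1.96) / 0.05 = 2.338.
- Observed standardised difference: 2.338 × √(1/60 + 1/20) = 2.338 × 0.2582 = 0.604.
- AUC: Φ(0.604/√2) = Φ(0.427) = 0.665.

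Simulation gives 0.67 for every m from 50 to 1000, and about 92% of selected noise metabolites have a 95% CI (Hanley–McNeil) wholly above 0.5. For comparison, the null standard error of the AUC is √(81 / (12 × 60 × 20)) = 0.075, so without selection only values beyond 0.5 + 1.96 × 0.075 = 0.647 would stand out. The average selected noise metabolite exceeds that.

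**3. Other forms the ROC might take (simulated, same noise).**

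| Quantity | Same samples | New samples, or selection repeated in each fold |
|---|---|---|
| Mean of selected single metabolites | 0.67 | 0.50 |
| Best single metabolite, m = 50 to 1000 | 0.69 to 0.75 | not run (true value 0.50) |
| Ten-metabolite panel, m = 200 | 0.92 | 0.49 (SD 0.12) |
| One-component PLS-DA score, m = 50 / 100 / 200 | 0.91 / 0.97 / above 0.99 | 0.50 |

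**4. AUC of selected noise, day 0 versus week 12.** With selection by a paired test, the standardised difference is 2.338 × √(2(1 − ρ)/60):
- ρ = 0: 0.427, AUC Φ(0.427/√2) = 0.62.
- ρ = 0.5: 0.302, AUC 0.58.
- ρ = 0.7: 0.234, AUC 0.57.

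Simulation agrees (0.57 to 0.62). With selection by the four-visit repeated measures ANOVA the mean AUC is 0.58 at ρ = 0, falling to 0.54 at ρ = 0.7. The share with a CI above 0.5 falls over the same range from 37% to 2% after ANOVA selection, and from 81% to 2% after paired selection.

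**5. Conditional check: selection on the day-0 PD–healthy difference, no treatment effect.**
- Share of the chance difference that sits in the PD mean: (1/60) / (1/60 + 1/20) = 0.25, so the PD mean is displaced by 0.25 × 0.604 = 0.151 SD.
- Expected later drift towards healthy: (1 − ρ) × 0.151, or 0.075 SD at ρ = 0.5.
- SD of the mean change at ρ = 0.5: √(0.5² × 0.75/60 + 0.75/60) = 0.125.
- Probability of moving towards healthy: Φ(0.0755/0.125) = Φ(0.604) = 73%, instead of 50%. The same formula gives 77% at ρ = 0.3 and 68% at ρ = 0.7.

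In simulation, false significance rises only modestly, to 7–10% with a paired test and 7–8% with the four-visit ANOVA, instead of 5%.

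**The case against.** The strongest reply is that the article is a condensed account. Cross-validation and permutation settings for PLS-DA commonly sit in a full protocol or analysis plan that is not shown, so their absence here is not an error. That stands, and the point does not rest on it. It rests on the role the text gives to the ROC and on the single cohort it describes. That the same samples serve both purposes is an inference from that cohort, and it would fall if the full plan separates selection from evaluation.

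The second reply is that the Sample Size section calls the study exploratory, that the primary outcome is the MDS-UPDRS, and that no decision hangs on the ROC. This lowers the severity. It does not rescue the word *confirm*, because an exploratory analysis cannot confirm its own selections.

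Four stronger readings are tempting, and the document does not support them:
- *The treatment ROC treats repeated samples of a patient as independent.* The text does not say so. It does not define the treatment classes, and the time-course test it names, repeated measures ANOVA, respects the pairing.
- *Selected metabolites will drift towards healthy.* This follows only if selection uses the day-0 PD–healthy contrast. The article never says that PLS-DA does the selecting, so this is a conditional risk.
- *The AUC will be near 1.* Those values belong to a whole PLS-DA score. The plan applies ROC to the selected metabolites, and for single ones the relevant figure is about 0.67.
- *Noise will be confirmed, and the AUC shows overfitting only.* No AUC cut-off is stated, and a strict one would reject most single noise metabolites. Where real differences exist, the same-sample AUC mixes discrimination with optimism.

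**Conclusion.** The point holds for the disease contrast. As written, with one cohort, an ROC for PD versus healthy on metabolites chosen for that contrast is circular. Pure noise would show a mean AUC of about 0.67 (best single metabolite 0.69 to 0.75, higher for panels or a PLS-DA score) against a true 0.50. For treatment the bias has the same direction but is smaller, 0.54 to 0.62, and at a within-patient correlation of 0.7 almost no selected noise metabolite has a CI clear of 0.5. The drift towards healthy is a risk only under one possible selection route.

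These sizes depend on the assumed P<.05 rule, and those for the best metabolite, panels and PLS-DA score also on the assumed number and independence of metabolites. The circularity itself depends on none of these. Severity is moderate: the analysis is exploratory and secondary, but the stated conclusion is one it cannot deliver.

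**What to change.** - Put scaling, feature selection and model fitting inside repeated stratified cross-validation, with all samples of a patient in the same fold.
- Compute ROC and AUC from out-of-fold predictions only, and give a label-permutation P value in which the whole procedure, selection included, is rerun for each permutation. With 20 healthy participants a five-fold split tests only 4 at a time, and the null SD of 0.12 above shows how imprecise one split is, hence the repeats.
- Replace *confirm* with wording such as: estimate internally validated discrimination. If cross-validation is not done, label any same-sample AUC as descriptive.
- For the time analysis, either choose features by a rule that does not use the day-0 PD–healthy contrast, or test all features with false discovery rate control.
- State the classes of the treatment ROC, and if they are pre and post, analyse them as paired.

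The cost is some programming and lower reported AUCs. No new samples are needed. Recruitment has ended and analysis is under way, so the choice should be recorded before the ROC results are seen.
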